**Figure 3. F3:**
[figure not shown]
Transition-free (or survival) probability by initial access state (hypothetical). This hypothetical survival plot displays how the probability of not reaching a given state can be graphed as a function of the initial state. In this example, the probability of not reaching behavioral treatment and counseling in an outpatient setting (not shown) is markedly higher when the incident substance use disorder event occurs in the emergency department setting, when compared to primary care or behavioral health settings. Potentially, this is suggestive of inefficiencies in referring people from emergency department settings to behavioral treatment and counseling in an outpatient setting.

What is the contribution of care states in achieving terminal states? We will calculate restricted mean survival times (RMSTs) [69] between a given SUD care state and each terminal state. An example of RMST quantities between select care states and a terminal state is presented in Table 5. The RMST captures the average terminal-event-free time, which in this study reflects time before reaching a terminal state, calculated as the area under the terminal-event-free curve over a prespecified time interval since the entry to the given care state. Figure 4 presents an example of terminal-event-free curve estimates using states from Figure 1. In this example, care types that produce lower RMSTs are those more likely to end in ceasing SUD care. Identifying these care types can inform targeted efforts, such as enhancing care coordination or improving staff levels in specific settings or for patients who receive certain treatment modalities to increase retention in SUD care.

**Table 5. T5:** Restricted mean survival times (RMST) from selected care types to ceasing care.

Substance use disorder (SUD) care state	Follow-up time (days)		
	30	60	90
Behavioral treatment and counseling, outpatient	μ₁,₄(30)^a^	μ₁,₄(60)	μ₁,₄(90)
Evaluation and assessment, intensive outpatient treatment	μ₂,₄(30)	μ₂,₄(60)	μ₂,₄(90)
Pharmacotherapy, outpatient	μ₃,₄(30)	μ₃,₄(60)	μ₃,₄(90)

a 𝜇_i_,_𝑗_(𝑡_𝑜_) is the restricted mean survival times from state i to state j over time interval 𝑡_𝑜_, where i=1 (behavioral health counseling, outpatient), 2 (evaluation and management, intensive outpatient treatment), and 3 (pharmacotherapy, outpatient); j=4 (ceasing substance use disorder care).

**Figure 4. F4:**
[figure not shown]
Transition-free (or survival) probability by care state (hypothetical). This hypothetical survival plot displays how the probability of not reaching a given terminal state can be graphed as a function of care states. In this example, the probability of not transitioning to the state of ceasing substance use disorder (SUD) care (not shown) is markedly higher for patients receiving behavioral treatment and counseling in inpatient or residential settings, when compared to patients receiving evaluation and assessment in an outpatient setting or pharmacotherapy in an intensive outpatient setting. Potentially, this can inform targeted efforts such as enhancing care coordination or improving staff levels in specific settings or for specific treatment modalities to increase retention in SUD care.

What are common sequences of care following each initial state? Care pathways consist of a sequence of transitions across care types and settings. To characterize these sequences, we will calculate the probabilities of all identified pathways starting from a given initial state in Table 1, proceeding through multiple care states, and ending in a specific terminal state. We will estimate probabilities of sequences of varying length. The length of sequences will be informed by descriptive analysis examining the mean and median number of transitions among subgroups of patients achieving terminal outcomes in Table 2. Sequence probabilities will be estimated using the fitted MSMs under hypothetical scenarios, such as repeated cycling between care and care-discontinuation and specified transition timings (see Multimedia Appendix 2).

How often and where is guideline-concordant care achieved? We will analyze several health care quality measures, including those published by the National Committee on Quality Assurance [36,70,71] and others [72,73]. These monitor initiation of care, or the receipt of prespecified health services following an incident SUD event; engagement in care, defined as having a minimum number of qualifying services after initiating care; and adequacy of treatment, which captures whether quantity or duration of treatment over time is sufficient. Achievement of these measures can be ascertained from the states in the MSM model. Multimedia Appendix 1 contains details about how we will operationalize these quality measures using estimates from the fitted MSMs. For example, a National Committee on Quality Assurance quality measure monitors follow-up for patients who have an acute care encounter for SUD. This measure monitors the percentage of patients who obtain follow-up SUD care after an ED visit over 7-day and 30-day timeframes. Thus, among patients in the ED and hospitalizations subcohort whose incident SUD event is in an ED setting, we will estimate transition probabilities capturing the likelihood of transitioning from the initial state to any SUD care state within 7-day or 30-day. We will estimate measures reflecting care engagement and adequacy of treatment by estimating the expected length of time in a pharmacotherapy state or the expected number of visits to qualifying states over the duration of time specified in Multimedia Appendix 1.

How does the probability of occupying terminal states differ across patient subgroups? Within study subcohorts, we will conduct descriptive analysis comparing occurrences of terminal states across patient subgroups. For instance, we will compare terminal states at selected time points (eg, 1-year after cohort entry) across mutually exclusive subgroups defined by patient SUD type (eg, sole opioid, alcohol, or cannabis use disorder vs multiple SUDs). Comparisons of terminal states will help provide insights into whether outcomes differ for specific groups of patients who have incident SUD events in each setting [28].

How do answers for the above key questions differ across patient characteristics? First, overall quantities will be estimated to address the key questions in Table 4. Then, Cox proportional hazards models will be fit for each transition intensity to assess associations between patient characteristics, such as demographics, SUD type and severity, mental health diagnosis, socioeconomic status, and transition intensities [9]. Using the fitted model, the quantities required to address the questions in Table 4 will be calculated as a function of patient characteristics included in the transition models.

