b Temporary discontinuation will be defined separately for each care state using an appropriate threshold for time elapsed between visits that reflects acceptable gaps in care for that specific state. All of these periods will be shorter than 194 days to distinguish temporary discontinuation from ceasing substance use disorder care.

c *DSM-5*: *Diagnostic and Statistical Manual of Mental Disorders, Fifth Edition*.

Terminal states indicate the end of an SUD care episode (Table 2), such as ceasing SUD care.

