### Statistical Analyses

#### Aim 1: Apply MSMs to Comprehensively Characterize SUD Care Transitions

Separate MSMs will be run for each of the 5 subcohorts specified in Table 1. The 5 subcohorts are mutually exclusive. All prespecified states that are anticipated will be considered. States may be collapsed to address states with a small number of events, and new states may emerge if they occur with sufficient frequency (eg, concurrent receipt of pharmacotherapy and behavioral treatment and counseling). When collapsing or expanding states, we will strike a balance between clinical interpretability and reliable parameter estimation. As a general guideline, ≥40‐50 transition events from *S*_*j*_ to *S_j_* per covariate helps ensure stable hazard ratio estimates and corresponding SEs, but if collapsing states compromises the clinical interpretability of the results, we will adopt a more permissive threshold of at least 10 transition events per covariate for modeling [58]. This criterion will first be applied to define states; specifically, a minimum of 40 (or 10 under the more permissive threshold) transition events is required to define a state, allowing inclusion of 1 covariate in the transition model. When transitions are sufficient to include covariates in the model, at least 40 × *m* transition events are required. Covariate selection for each transition model, given the number of transitions, is described below. Follow-up time or care episode duration is defined as the interval from entry into the initial state (time 0) to entry into a terminal state.

Figure 1 provides a graphical representation of a simplified MSM illustrating potential care pathways. In this example, patients who meet the inclusion criteria and are identified as having an incident SUD in primary care enter the initial state *C*_1_. Patients then transit into 1 of 15 care states (*S*_1_, ... ,*S*_15_) defined by a service type and setting. From these states, patients may transition to temporary discontinuation of care, *D*, or an SUD remission state, *R*. Transitions between the transient states (care states, temporary discontinuation, and SUD remission) are bidirectional, whereas any transition to a terminal state (*T*_1_, ..., *T*_4_) is unidirectional, reflecting that patients cannot leave terminal states once they are entered in MSMs. At the end of follow-up, patients occupy 1 of the 4 terminal states.

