For simplicity, we omit transition-specific subscripts for the parameters $\left(\eta ,k_{0},\beta \right)$. In the model, $s(\log(t)|\eta ,k_{0})=\sum_{i=1}^{k_{0}}\eta_{i}B_{i}(\log(t))$ represents the log cumulative baseline intensity function, which we model flexibly using restricted cubic spline basis functions (also known as natural cubic splines) $B_{i}(\cdot )$, with corresponding coefficients $\eta_{i}$. The number of knots, $k_{0}$, determines the number of basis functions and thus the flexibility of the baseline intensity functions. For covariates *z*_*i*_(*t*), the coefficients β represent the log hazard ratios at time t. The unknown parameters to be estimated or selected from data are $\left(\eta ,k_{0},\beta \right)$. We will use the Akaike information criterion based on data to select the number of knots, with lower Akaike information criterion values indicating better model fit. The regression coefficient parameters (η,β) will be estimated by using the maximum likelihood approach for statistical inference [62,63]. For each transition, we will include prespecified covariates for adjustment when the number of transitions allows (at least 10 transition events per covariate), and if additional covariate selection is required, variables that are statistically significant at the 5% level based on Wald tests will be included [64]. The estimated transition intensities are transformed to a transition probability from states j to k at time t since entry into state j at time s (s<t, s and *t*>0), by integrating, $p_{jk}(s,t)=\exp\left\{-\int_{s}^{t}q_{jk}(u,z(u))\;du\right\}$.

Multiple incident SUD events may be observed within the same patient (see Quantitative Study Population). For example, a patient may have an incident SUD event, eventually experience a terminal state such as ceasing SUD care (eg, one who receives no SUD care for 194 days), and then experience a second incident SUD event. Including multiple incident events from the same patient within the same subcohort in the MSM framework may introduce within-patient correlation and reflect care pathways that differ from those of the initial episode. We will account for within-patient correlation using a sandwich variance estimator for the parameter estimates. The number of prior incident events will be included as a covariate or used as a stratification factor, depending on its distribution.

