Table 4 summarizes estimates that can be obtained from fitted MSMs to generate our inferences and answer additional research questions. We will calculate point estimates and CIs and further characterize variation in output quantities across states graphically.

**Table 4. T4:** Summary of multistate model output quantities.

Output	Description	Example question answered
Intensity matrix	Instantaneous probability of moving from 1 state to another	How likely is a transition from an initial primary care state to a behavioral treatment and counseling care state over a small incremental unit of time?
Transition probability matrix	Probability of moving from 1 state to another over a specific time duration	What is the probability of moving from an initial primary care state to a behavioral treatment and counseling care state within 14 days of SUD^a^ identification?
Hitting probability	Point estimate of the probability of ever reaching a state	What is the probability of ever reaching pharmacotherapy during a care episode?
Mean sojourn time	Mean length of time a patient stays in a state	On average, how long does a patient stay in the evaluation and assessment care state before transitioning to another state?
Restricted mean transition-free time	Mean length of time a patient spends in transient states before reaching a terminal state	What is the average time before a patient ceases SUD care after receiving pharmacotherapy?
Expected first passage time	Expected days until hitting a specific state of a set of states	How long until a patient receives SUD pharmacotherapy?
Expected number of visits	Expected number of times a state is reached between 2 given times	What is the predicted number of times behavioral treatment and counseling are reached in the first 30 days of a care episode?
Survival plot	Probability of not reaching a state, as a function of time	How is the probability of not ceasing SUD care after their index SUD event?

a SUD: substance use disorder.

How does the accessibility of each state vary? We will use the models to describe how the accessibility of each state varies by estimating the dynamics of transitioning between different types of care for SUD. We will report and characterize variation in (1) transition probabilities, (2) hitting probabilities, (3) mean sojourn time, (4) expected first passage time, and (5) expected number of visits (definitions in Table 4).

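### The 7-day and 30-day ED follow-up measure, and the 14-day example in Table 4, are first-entry-by-day-t quantities, but the plan assigns them to transition probabilities, whose index and printed formula describe something else

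*Protocol article*

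**What the plan says.** Under Aim 2, in the paragraph on guideline-concordant care, the article describes the national quality measure: "This measure monitors the percentage of patients who obtain follow-up SUD care after an ED visit over 7-day and 30-day timeframes". For ED patients it then names the estimator: "we will estimate transition probabilities capturing the likelihood of transitioning from the initial state to any SUD care state within 7-day or 30-day".

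Table 4 describes the transition probability matrix as "Probability of moving from 1 state to another over a specific time duration". Its example asks for the chance of moving from the initial primary care state to behavioral counseling within 14 days of identification.

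The only formal definition is under Aim 1, after the model equation. There the intensities are "transformed to a transition probability from states j to k at time t since entry into state j", and the expression that follows begins "p_{jk}(s,t)=\exp\left\{-\int_{s}^{t}q_{jk}(u,z(u))\;du", that is, the exponential of minus the integrated j-to-k intensity.

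Three other statements matter:

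- Aim 1 allows patients to leave care states: "Transitions between the transient states (care states, temporary discontinuation, and SUD remission) are bidirectional".
- Table 2, footnote b, gives only an upper limit for the gaps that define temporary discontinuation: "All of these periods will be shorter than 194 days to distinguish temporary discontinuation from ceasing substance use disorder care".
- Table 4 also lists a survival plot, described as "Probability of not reaching a state, as a function of time".

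**The concern.** The target is an event by day t. The named tool, in ordinary multistate usage, is a state at day t. The two agree only when the qualifying states cannot be left, and here they can. A patient who attends on day 3 and by day 30 is in discontinuation, remission or a terminal state has met the ED measure but is not in care on day 30. For one named care state, a patient who has moved on to another kind of care is also missed.

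The initiation and follow-up results are among the study's guideline-concordance findings. The last key question of Aim 2 also recalculates the Table 4 quantities by patient characteristics. If the occupancy version were computed, a subgroup that starts care equally often but moves on faster would look as if it started less often.

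**Working it through.** The article states no value for these measures, so there is no figure to reproduce. The check compares three quantities that the text could mean:

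- F(t): probability that a qualifying care state has been entered by day t. This is the target.
- O(t): probability of being in a qualifying care state on day t. This is the standard transition probability, summed over qualifying states.
- N(t) = exp(−∫q): the printed formula.

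**Step 1, direction of O.** Anyone in care on day t has entered care by day t, so O(t) ≤ F(t) always. They are equal only if nobody has left by t without returning.

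**Step 2, the printed formula.** N equals 1 at the start and falls with time, so it gives a lower value at day 30 than at day 7. A follow-up measure must rise. N is the probability of *not* having made that one transition, ignoring other exits.

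**Step 3, any-care measure with exits from the first day.** All rates are assumed. States are initial, any care (pooled), discontinued or remitted, and terminal. Entry rate is a per day, mean stay in care m days, return rate 1/60 per day, and terminal rate x = 0.0005 per day from every non-terminal state.

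F(t) = a/(a+x) × [1 − exp(−(a+x)t)], with a solved to give the assumed F(30). O(t) is the initial-to-care entry of exp(Qt). N(t) = exp(−at). Ranges are for m = 14 to 90 days.

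| Assumed F(30) | a | F(7) | O(7) | O(30) | N(7) | N(30) |
|---|---|---|---|---|---|---|
| 20% | 0.00750 | 5.1% | 4.0–4.9% | 9.2–17.2% | 94.9% | 79.9% |
| 35% | 0.01448 | 9.6% | 7.6–9.3% | 15.6–30.0% | 90.4% | 64.8% |
| 50% | 0.02333 | 15.0% | 11.8–14.5% | 21.6–42.6% | 84.9% | 49.7% |

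At day 30, 1 − N is 20.1%, 35.2% and 50.3%. That is close to the target and slightly above it, because competing exits are ignored.

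**Step 4, any-care measure with a gap threshold, as Table 2 requires.** Assume F(30) = 35%, no competing exits, 40% of entrants with a single visit, and discontinuation dated g days after that visit. Then a = −ln(0.65)/30 = 0.01436 and O(t) = F(t) − 0.4 × F(t − g).

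- g = 0: 35.0 − 0.4 × 35.0 = 21.0%
- g = 7: 35.0 − 0.4 × 28.1 = 23.7%
- g = 14: 35.0 − 0.4 × 20.5 = 26.8%
- g = 30 or more: 35.0 − 0 = 35.0%, no loss

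At day 7, F is 9.6%. O is 5.7% with g = 0 and 9.6% once g is 7 or more.

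**Step 5, one named care state by day 14 (the Table 4 example), with no discontinuation.** Assume entry at 0.01 per day to each of two care states, switching between them at h per day, and terminal rate 0.0005 per day. By symmetry O(14) = ½ × exp(−0.007) × [1 − exp(−0.28)] = 12.1% for every h. The target, with the named state made absorbing, is:

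- h = 0.02: 13.8%
- h = 0.05: 15.7%
- h = 0.10: 18.0%

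Access to the named service changes across these settings while the occupancy figure does not move.

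**The case against.** The strongest reply is that the article never says its transition probability counts patients who are in care on the day. Its wording for the ED measure and in Table 4 speaks of moving within a window, which is the right target. Where it means occupancy, in the stacked-plot question, it says occupancy. The printed formula is not occupancy, and taken literally it would overstate follow-up at a true 20% or 35%. The right curve is already planned: Figure 3 illustrates not reaching a care state from the ED. Finally, the article sends the operational detail to Multimedia Appendix 1, which is not shown.

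Most of this stands. A reader might infer that the plan fixes an occupancy estimator and will understate follow-up by some definite number of points. The documents do not support that. They give neither rates nor discontinuation thresholds. Ceasing care needs more than 194 days without services, so it adds no exits by day 30 if dated when that gap is met. Movement between care states costs the any-care measure nothing.

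It does not remove the point. The informal wording, the time-t index and the formula describe three different quantities, and only the informal wording matches the measure. The survival curve that would give the answer is listed separately and is not assigned to these measures. Thresholds also offer no protection in the Table 4 example, nor against exits to remission, which need no gap in care.

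**Conclusion.** The point holds as a mismatch between measure and named estimator in the article's own text. A by-day-t measure is assigned to transition probabilities, and neither the standard meaning of that term nor the printed formula gives first entry by day t.

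The consequence is conditional. If the standard occupancy version is computed, the result cannot be too high and may be too low. For any care after an ED visit, the loss through discontinuation ranges from near zero, with thresholds as long as the window, to substantial, with early exits. At day 7 it is at most about 3 points under the rates of Step 3, and nil in Step 4 once the threshold reaches 7 days. For a single named care state some loss is expected wherever patients switch services within the window. All percentages rest on assumed rates and are illustrations, not estimates of bias in this study. Multimedia Appendix 1 may already settle the ED measure.

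**What to change.** In the guideline-concordant care paragraph and in Table 4, define every measure with a day limit as the cumulative incidence of first entry to the qualifying care state(s) by day t. Make the qualifying states absorbing for this calculation and keep the other exits as competing events. This equals one minus the plan's own curve for not reaching a state, provided that patients who leave by a competing exit stay in the not-reached group and are not censored.

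Replace the 14-day example in Table 4 with an occupancy question, or move it to the survival-plot row. Keep transition and occupancy probabilities for the stacked plot. Bring the definition under Aim 1 into line with whichever quantity is meant, and align Multimedia Appendix 1 if it differs.

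The cost is wording plus a small change to the output code. No transition model needs refitting.

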#### Aim 3. Observe and Explore Patient and Clinician Experiences With Care Transitions Across Common Care Pathways Using Qualitative Research Methods

Aim 3 includes observations and interviews to explore the context for SUD care decisions and experiences with SUD care transitions. We will perform direct observations [74,75] of patient-clinician encounters during salient SUD visits, such as behavioral health intake visits. Witnessing and documenting these interactions will provide key information on decision-making regarding various clinical scenarios. We will also conduct semistructured in-depth interviews with a broad sample of patients and clinicians to collect views, preferences, and needs of individuals engaged in different care pathways. Observations and interviews will be concurrent to inform ongoing data collection and confirm data sufficiency [76]. We will draw on phenomenological [77] and ethnographic theory [78] to explore emic [79], or insider perspectives on care transitions.

The quantitative and qualitative components synergize in 2 ways: first, by using an explanatory sequential sampling mixed methods design [80] whereby qualitative interview participants are purposely sampled from potentially meaningfully rich subgroups of patients who have embarked on specific care pathways identified in the quantitative population. Second, by integrating quantitative and qualitative data in the analysis phase. Specifically, we will reapply the inclusion criteria for aims 1 and 2 to identify patients who were recently identified to start an episode of SUD care at the time of qualitative data collection. We will then match the patient’s observed sequence of care to model-identified pathways estimated in aim 1. We will then purposively sample [81] patients from six pathways: (1) two of the overall most common care pathways, (2) two of the most common care pathways that contain guideline-concordant care, and (3) two of the most common care pathways that have a high probability of reaching negative terminal states (eg, death). We will be open to the emergence of other important care patterns to guide our sample selection, and we may consider other important factors, such as SUD type and/or severity, when defining these groups. We will sample approximately 3‐5 patients from each pathway (estimated to be 35 patients) and ensure representation across demographic groups and those with different SUD types.

For the patient interviews, a semistructured interview guide will include three main topics: (1) care choices and constraints at critical junctures (eg, referral to specialty services), (2) care alignment with patient needs and preferences (eg, care frequency and location), and (3) clinical and care quality outcomes (eg, treatment adequacy). Interviews will use a modified form of free listing [82-84], an ethnographic technique increasingly used in health research [85-87] to elicit insider views and conceptions of a cultural or experiential domain (eg, process of obtaining SUD care). We will ask patients to rapidly say or write words that come to mind when thinking of an experience (eg, patient decision-making). Their words are assumed to indicate salient constructs within a domain (eg, treatment options) common to people who share the experience and help reveal the conceptual boundaries of the domain of interest. This provides a foundation for further inquiry into health-related experiences, attitudes, beliefs, and behaviors [88]. We will query how patients conceive of and define care journeys, potential choices, and instructions from clinicians. We will draw from the Chronic Care Model [29] to inquire how the free-listed words affected the ability to achieve outcomes, and how clinicians and systems can better support care transitions.

For clinician interviews, we will interview employees of KPWA or external organizations in the contracted care network who help patients make SUD care decisions in primary care, ED, urgent care, behavioral health, and specialty SUD care. We will oversample clinicians who provide care in roles that are consistent with the model-identified common care pathways and ensure representation across clinician disciplines and care settings. We will recruit clinicians over email to arrange a video interview [89]. We anticipate recruiting approximately 25 clinicians. Guided by the Chronic Care Model, interviews will focus on decision-making and system- and practice-level factors affecting quality and coordination of SUD services. Questions will consider practice guidelines and information systems used to determine treatment plans, and how delivery system design affects referral choices. Per relevant literature, we will probe barriers and facilitators to care coordination (eg, program capacity), patient engagement, and meeting care needs. We will query beliefs and experiences tied to the role clinicians play in enhancing care continuity, and how roles can be strengthened [90]. All interviews will be conducted by phone or videoconference platform, recorded, and professionally transcribed.

We will also conduct patient-clinician observations during visits where SUD treatment planning takes place, such as scheduled SUD intake evaluations, primary care visits that follow ED or inpatient discharge, addiction psychiatry consultation, and buprenorphine induction. We will conduct up to 20 observations (≈5 per visit type), monitoring for data saturation, to capture nuances of the patient experience at critical transition points [91]. We will contact clinicians via email to invite them to have their visits observed. When a clinician agrees, a researcher will be available when the clinician begins the scheduled video or phone-based session. The clinician will ask the patient if a researcher could join to observe. If the patient agrees, the researcher will join the video call, invite the patient to participate in study observations, and obtain verbal informed consent. A semistructured observation template will be developed for taking field notes to document the context in which care options are considered and decided upon, and assess multilevel factors affecting care planning and pathways pursued. The template will be organized by the Chronic Care Model constructs and allow for unstructured notes and reflections. After each data collection (interview or observation), qualitative researchers complete a structured memo to identify data gaps and challenge assumptions. Prompts such as “what surprised you” and “what is unanswered” help the researcher reflect on initial assumptions and reveal data gaps to explore. After 5 data collections, memos are summarized and discussed to monitor data quality and completeness. Physician and social work investigators, partners, and consultants will join debriefs as data collection unfolds to identify new questions to be pursued.

A total of 2 researchers will analyze all qualitative data using thematic analysis [92]. We will code transcripts and observation notes using deductive and inductive codes [93]. The initial code list will be developed from interview and observation guide questions and prompts and Chronic Care Model domains. Inductive codes will be developed from reading transcripts and notes. Further, 2 researchers will read the same subset of transcripts to derive emergent codes, discussing and resolving discrepancies by consensus. We will combine all the codes, refine the code list via an iterative process, and rely on the Atlas Ti qualitative platform [94] to apply the final codes to transcripts and observation notes. Lastly, we will examine the coded text to highlight key themes and subthemes and use coding memos to summarize and further refine themes. Coding memos will form the basis for disseminating study results. We estimate that our patient and clinician samples will ensure the analytic depth, rigor, and trustworthiness of the findings, but we will monitor thematic saturation during analysis and recruit additional participants if needed [91,95]. We will triangulate interview and observation data to interrogate qualitative findings [96,97] and reach robust conclusions. Then we will integrate qualitative and quantitative findings by constructing a joint display of key qualitative themes and salient estimated quantities [80]. The joint display will highlight patterns, reveal concordant or discordant findings, and expand overall interpretation [98].

